### 2.3. Study procedures and visit schedule

Participants will be recruited consecutively according to eligibility criteria. Patients will be invited by physicians from the research team during routine clinical practice. Healthy controls will be invited by members of the research team and, if they agree to participate, will be referred to a physician from the research team for baseline assessment. As this is an observational study, no randomization or blinding procedures will be applied.

At the baseline visit (V0), all participants will receive verbal and written information about the study objectives, methodology, non-invasive nature of the procedures, confidentiality safeguards, and exclusive research use of the collected data. Written informed consent will be obtained before any study-related procedure. A clinical interview will then be conducted to collect baseline sociodemographic and clinical information, followed by psychometric assessment using the clinical instruments specified in the protocol. During the same session, voice recordings will be obtained under standardized conditions.

Only patients with depressive disorder will undergo longitudinal follow-up. Patients will attend four additional visits coinciding, whenever possible, with routine psychiatric follow-up visits: V1 at 30 days, V2 at 60 days, V3 at 90 days and V4 at 120 days, each with an allowed window of ±7 days. At each follow-up visit, the same recording and clinical assessment procedures applied at baseline will be repeated. Clinician-rated and self-reported measures of depressive severity will be updated, and relevant clinical changes, including treatment adjustments or adverse events, will be documented. Healthy controls will complete only the baseline visit under the same recording conditions.

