In all participants, data collection will be integrated into the clinical interview. Only the part of the medical interview corresponding to the MADRS assessment will be audio recorded. In order to combine open ended questions by clinicians that allow patients to describe their experiences in their own words, allowing spontaneous and elaborated responses, while adopting a reliable method of exploration, the instructions of Montgomery and Asberg for the MADRS will be adopted, moving from broadly phrased questions about each symptom to more detailed ones which allow a precise rating of severity [27]. The recorded material will comprise the complete MADRS-related clinical interaction, including an initial free-speech segment immediately followed by the semi-structured questions used to complete the scale. The free-speech segment will be an introductory part of the recorded MADRS assessment (namely, patients will be asked to describe, in their own words, how they have been feeling in the past week). This recorded segment is expected to last approximately 10–30 minutes including the initial free-speech segment, allowing voice and speech to be collected within a clinically meaningful interaction while maintaining a standardized procedure.

Voice recordings will be assigned a pseudonymized audio identifier linked to participant type, participant code and visit number. Any relevant recording incident, including interruption due to patient need, clinical need or technical problems, will be documented in the case report form and considered in data quality assessment.

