### 2.5. Voice recording protocol

Voice recordings will be obtained using a Jabra Speak 510 USB omnidirectional microphone, positioned frontally at a distance of no more than 20 cm from the participant’s mouth. Recordings will be conducted in a quiet hospital room, with minimized background noise, closed doors and windows whenever feasible, silenced electronic devices, and no overlapping speech or external interruptions whenever possible.

The Jabra Speak 510 microphone was selected for pragmatic and translational reasons: it is affordable, widely available, easy to deploy and compatible with routine hospital use. This choice prioritizes ecological validity over laboratory-grade audio fidelity, which may reduce the precision of signal-sensitive measures such as jitter, shimmer, HNR, and intensity. This potential variability will be reduced by maintaining the same microphone, configuration, placement, and recording conditions throughout the study. This approach is consistent with previous studies that have used non-specialized recording devices, including tablet microphones, smartphone microphones and mobile phones, to extract clinically relevant speech and voice features [19,24,25,30].

Repeated assessments will be scheduled within a similar time-of-day window for each participant whenever feasible. Because recordings are integrated into routine clinical visits, exact consistency cannot be guaranteed; recording time will therefore be documented and considered in sensitivity analyses. Audio recordings will be stored in uncompressed WAV format to preserve signal integrity during feature extraction. All files will be labeled using pseudonymized alphanumeric identifiers. Speaker diarization will identify participant and interviewer segments, followed by manual review. Overlapping or uncertain segments will be excluded, and the original recording will be preserved unchanged. For acoustic and paralinguistic analyses, only participant speech will be retained. The complete interaction will be automatically transcribed and manually reviewed to correct transcription and speaker-attribution errors. Linguistic variables and contextual text embeddings will be extracted from the reviewed participant transcripts, while interviewer turns will be retained as conversational context.

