Neurostimulation variables	Receipt of electroconvulsive therapy in the current episode, type of electroconvulsive therapy, and other neurostimulation treatments	V0–V4 in patients

**Table 3 pone.0353827.t003:** Multimodal voice- and speech-derived variables predefined in the VOICE-DEP protocol.

Domain	Variable/ group of variables	Operationalization/ measurement
Acoustic	Pitch	F0 mean, standard deviation and range (Hz).
	Energy/ intensity	Mean and standard deviation (dB).
	MFCCs	Coefficients 1–13 summarized by mean and standard deviation.
	Harmonic-to-noise ratio	dB.
	Jitter	Percentage (%).
	Shimmer	Percentage (%).
	Spectral descriptors	Spectral centroid, roll-off and slope (Hz or normalized units).
	Formants	F1–F3 mean frequency and bandwidth (Hz).
	Spectral/ prosodic entropy	Dimensionless entropy index.
	Embedding-based acoustic features	High-dimensional vector representations derived from pretrained models (e.g., Wav2Vec2, HuBERT).
Paralinguistic	Speech rate/ articulation rate/ pause duration	Words per second and pause duration in seconds.
	Prosodic range	F0 and intensity variability (Hz, dB, or coefficient of variation).
	Pause ratio	Silence-to-speech proportion (0–1 or %).
Linguistic	Sentiment polarity	Continuous score from −1 to +1.
	Negative emotional word ratio	Percentage (%) of negatively valenced words.
	First-person singular pronouns	Percentage (%) or frequency per 100 words.
	Lexical diversity	MTLD, Honor´e and type-token ratio.
	Word count/ mean sentence length	Number of words and words per sentence.
	Lexical sentiment variance	Standard deviation of sentiment scores.
	Lexical coherence/ cohesion	Cosine similarity based on semantic embeddings.
	Contextual text embeddings	High-dimensional representations extracted from a pretrained open-weight language model.

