For diagnostic discrimination between patients and healthy controls, classification models will be developed and evaluated. The area under the receiver operating characteristic curve (AUC) will be used as the principal performance metric, and additional measures such as odds ratios and their corresponding 95% confidence intervals will be reported where applicable. These analyses will be interpreted as exploratory because the study is a pilot methodological validation study rather than a definitive diagnostic accuracy trial.

Third, a systematic comparison between unimodal and multimodal approaches will be conducted. Unimodal models will include models based exclusively on audio-derived features or text-derived features, whereas multimodal models will combine acoustic, paralinguistic, and linguistic information. This comparison is intended to quantify the added value of multimodal integration beyond individual feature domains and is directly aligned with one of the predefined secondary objectives of the study.

Embedding-based acoustic features and contextual text embeddings will be evaluated exploratorily because previous studies suggest that they may capture clinically relevant patterns beyond predefined features [8,10,12,13]. Given their high dimensionality and limited interpretability, they will not constitute the primary analytical approach. Model specifications and extraction procedures will be fully documented to ensure transparency and reproducibility.

Longitudinal analyses will be used to evaluate the evolution of voice- and speech-derived digital biomarkers over time and their association with changes in depressive symptom severity and global clinical status. Because repeated assessments are obtained in the patient group at V0, V1, V2, V3, and V4, these analyses will account for within-subject correlation. Mixed-effects models and, where appropriate, finite-difference or change-score approaches will be used to examine intra-individual trajectories and their relationship with variation in MADRS, CGI, and PHQ-9 scores, as well as with relevant treatment-related variables. Treatment exposure and changes during follow-up will be included, where feasible, as time-varying covariates in the mixed-effects models. Treatment-specific analyses will be considered exploratory and will not be interpreted causally.

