The study is conducted in a single clinical center and focuses on Spanish-speaking participants, which may induce selection bias and restrict external validity across healthcare systems, dialects, or linguistic contexts. Dialectal variation across Spanish-speaking regions may influence acoustic, prosodic, and linguistic characteristics. Therefore, the findings will be interpreted within the linguistic and geographical context of the study population and will require future external validation in samples from other Spanish-speaking regions and sociolinguistic settings. However, this focus also addresses a relevant gap in the literature, which has been predominantly centered on English-language datasets.

Because of the observational design and treatment heterogeneity, changes in speech cannot be fully disentangled from the effects of specific treatments. Treatment-related analyses will therefore remain exploratory and will not support causal inference.

Residual variability related to the recording time of the day will be acknowledged as a study limitation.

Finally, clinician-administered scales are used as the primary reference standards, but they are themselves subject to measurement variability and do not constitute an objective ground truth. In addition, symptom-focused MADRS questions may influence some linguistic variables, particularly sentiment-related measures, which will therefore be interpreted cautiously. The present protocol does not aim to replace clinical judgment but rather to complement it by identifying speech-derived markers that correlate with established measures of depressive severity.

In summary, the formal clinical diagnosis will define the study groups, whereas the MADRS, CGI, and PHQ-9 will be used to quantify symptom severity and longitudinal change. Speech-derived measures will therefore be interpreted as complementary correlates of clinical assessment rather than as independent objective standards, under the premise of supporting, but not replacing, the clinical judgment.

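### Section 2.5 does not keep interviewer turns out of the language-model input, so contextual text embeddings, and possibly lexical coherence, could carry the unblinded clinician's questions

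*Protocol article*

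**What the plan says.** Section 2.5 of the protocol article treats audio and text differently. For audio: "For acoustic and paralinguistic analyses, only participant speech will be retained". For text, the whole interaction is transcribed and checked, and then: "Linguistic variables and contextual text embeddings will be extracted from the reviewed participant transcripts, while interviewer turns will be retained as conversational context". What the retained context is used for is not stated.

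Table 3 (Section 2.6) defines the contextual text embeddings as "High-dimensional representations extracted from a pretrained open-weight language model", without saying what text the model receives. The same table defines lexical coherence through similarity of semantic embeddings.

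The source of the interviewer's words is described in Section 2.3. On what is recorded: "The recorded material will comprise the complete MADRS-related clinical interaction, including an initial free-speech segment". On how the questions proceed: "moving from broadly phrased questions about each symptom to more detailed ones which allow a precise rating of severity". On masking: "no randomization or blinding procedures will be applied".

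Section 2.7 makes both embedding groups exploratory ("they will not constitute the primary analytical approach") and names regularized logistic regression as the primary classifier. Section 3.1 warns that "symptom-focused MADRS questions may influence some linguistic variables, particularly sentiment-related measures, which will therefore be interpreted cautiously".

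**The concern.** A contextual language model computes the representation of each word from all the text in its window. If a clinician's question stands in that window, the vector for the participant's reply depends partly on the question, even when only the participant's words are pooled afterwards. The feature would then be labelled as participant speech but would partly describe the interviewer.

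This matters because the interviewer is not a neutral source. The clinician is not blinded, and the questions are asked in order to produce the MADRS score, which is one of the clinical reference measures. A text model could therefore appear to separate patients from controls, or to follow severity, partly by reading the questioning. The results at stake are the exploratory embedding models, their correlations with severity, and the secondary objective on the added value of multimodal over unimodal models.

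**Working it through.** The plan gives no figure on this point to reproduce, so the check is mainly a reading of the passages against one another.

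1. **Is interviewer text excluded from the model input?** For audio, yes: Section 2.5 keeps participant speech alone. For text, the features are drawn from participant transcripts, but the same sentence keeps interviewer turns as context. Neither Table 3 nor Section 2.7 closes the gap. The plan permits interviewer turns in the window; it does not prescribe them.

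2. **Which features could be exposed?**

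| Feature (Table 3) | Direct route for interviewer text? |
|---|---|
| Pronoun rate, word count, sentence length, lexical diversity, negative-word ratio | No, if computed on participant transcripts |
| Contextual text embeddings | Yes, if interviewer turns are in the window |
| Lexical coherence (embedding similarity) | Possibly, if interviewer turns are in the window or in the text compared |
| Acoustic and paralinguistic features | No; participant speech only |

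3. **Is interviewer text plausibly linked to group and severity?** Section 2.3 states that there is no blinding, that the recording is the MADRS interview, and that questions go from general to detailed in order to rate each symptom. Section 2.6 has MADRS assessed concurrently with the recording. It is an inference, not a stated fact, that more probing occurs where symptoms are reported.

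4. **Do the existing safeguards cover it?** Participant-level splitting and Leave-One-Group-Out cross-validation (Section 2.7) stop recordings of one person from falling on both sides of a split. A cue in how interviewers question patients and controls would be present in training and test participants alike, so splitting leaves it in place. The caveat in Section 3.1 concerns the effect of questions on the linguistic measures. It offers cautious interpretation and does not address interviewer text entering a feature.

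5. **Which way would the results move?** The embedding-based text model and the multimodal model would both tend to rise relative to audio alone. Because the text-only comparator rises too, the gain of multimodal over text alone could move either way.

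6. **Illustration of the mechanism only.** Take a score equal to a participant component (SD 1, no group difference) plus w times an interviewer component (SD 1, group difference D). Then AUC = Φ( wD / √(1 + w²) / √2 ). For D = 1.5 and w = 0.5: 0.75 / 1.118 = 0.671; 0.671 / 1.414 = 0.474; Φ(0.474) = 0.68.

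| D | w = 0.25 | w = 0.5 | w = 1.0 |
|---|---|---|---|
| 1.0 | 0.57 | 0.62 | 0.69 |
| 1.5 | 0.60 | 0.68 | 0.77 |
| 2.0 | 0.63 | 0.74 | 0.84 |

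Both D and w are assumed. The starting point, with no signal in participant text (AUC 0.50), is unrealistic for people describing their own symptoms. The table shows that a questioning cue alone can lift an AUC. It does not size the effect in this study, where the relevant quantity is the increment over participant-only text.

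**The case against.** The strongest reply is that Section 2.5 already names the source of the text features as the participant transcripts. On that reading, interviewer turns stay in the file so that a reviewer can follow the exchange and check who spoke. A journal article may also leave the content of an input window to a fuller document, and Section 2.7 promises full documentation of the extraction procedures. Embeddings are exploratory, all classifier results are presented as hypothesis-generating, and giving the model the question is a legitimate choice because a one-word answer means little without it.

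Much of this stands. The harmless reading is possible, the count-based variables are not directly exposed, and the consequence is confined mainly to exploratory analyses. What does not stand is that nothing needs changing. The article does address interviewer turns, and it does so in the sentence that defines the contextual embeddings, without the restriction it sets for audio. Documenting an extraction procedure does not remove a cue from it. Lexical coherence is also listed as a predefined linguistic variable, outside the two groups that Section 2.7 makes exploratory.

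A reader might infer more: that interviewer speech is a stated input to all linguistic features, that the embeddings therefore measure the interviewer, or that the primary classifier is compromised. The documents support none of these. Nor do they state that clinicians probe patients more than controls; Section 2.3 describes one procedure for all participants.

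**Conclusion.** The point holds in a limited, conditional form. As written, the plan allows interviewer turns into the language-model window. If they are there, the contextual text embeddings, and possibly lexical coherence, can carry questions plausibly related to group and MADRS score, and neither the data splitting nor the stated caveat would remove that.

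The consequence would be optimism in the exploratory text and multimodal embedding results and a distorted unimodal-versus-multimodal comparison. The primary regularized logistic regression on predefined features is largely unaffected, with coherence as its one possible exposure. The size cannot be estimated from the documents. The conclusion rests on two assumptions: that the retained context is used as model input, and that questioning differs with symptoms. It merits a change to the text because the protection is cheap under either reading.

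**What to change.** In Section 2.5, state that contextual text embeddings and lexical coherence in the main text analyses are computed from participant turns only, and that interviewer turns are kept solely for transcript review and speaker attribution. If the team also wants a version with the question in the window, report it only as a sensitivity analysis beside the participant-only result. Fit the same classifier, with the same splits, to interviewer turns alone and report its AUC as a benchmark for how much the questioning by itself distinguishes the groups.

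The cost is a short change to the text and one extra model run on transcripts already planned, with no new data. The drawback is that very short answers carry less meaning without the question; the optional context version would show how much that matters, read against the interviewer-only benchmark.

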### 2.4. Sample size and sampling strategy

The planned study sample comprises 75 participants: 25 patients with a clinical diagnosis of moderate or severe unipolar depression and 50 healthy controls. Patients will be assessed at five time points: baseline (V0) and four monthly follow-up visits at 30, 60, 90 and 120 days, each with an allowed window of ±7 days. Assuming complete follow-up, this will generate 125 longitudinal voice recordings in the clinical group. Healthy controls will undergo a single baseline assessment, generating 50 voice recordings. The planned dataset therefore comprises 175 voice recordings.

The sample size was defined pragmatically as a feasible recruitment target for a hospital-based feasibility and methodological pilot study conducted in a real-world clinical setting. The study is not intended as a definitive diagnostic accuracy trial powered to estimate the performance of a final clinical classifier. Rather, it is designed to evaluate the feasibility, standardization, reproducibility and analytical validity of a multimodal voice- and speech-based methodology for depression assessment and longitudinal monitoring.

As a quantitative sensitivity analysis, a baseline comparison of 25 patients and 50 healthy controls, with a two-sided significance level of 0.05 and 80% power, would detect a standardized mean difference of approximately Cohen’s d = 0.70. The study is therefore primarily sensitive to moderate-to-large effects. This is presented as a sensitivity analysis because reliable prospective effect-size estimates are not available for the multiple exploratory speech-derived variables included.

The sampling strategy will be consecutive and non-probabilistic. Eligible patients will be recruited during routine clinical care in the Department of Psychiatry, including both outpatient consultations and inpatient care. Healthy controls will be invited by members of the research team and assessed after confirmation of eligibility.

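### Text models that use contextual embeddings can classify partly on stated patient status, and no planned analysis separates that from depressed language

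*Protocol article*

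**What the plan says.** **Recording.** Section 2.3 limits the recording to the depression-scale part of the interview: "Only the part of the medical interview corresponding to the MADRS assessment will be audio recorded". It opens with free speech, in which "patients will be asked to describe, in their own words, how they have been feeling in the past week", and continues with the semi-structured scale questions.

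**Text source.** Under section 2.5 the whole interaction is transcribed automatically and then "manually reviewed to correct transcription and speaker-attribution errors". From there, "Linguistic variables and contextual text embeddings will be extracted from the reviewed participant transcripts", "while interviewer turns will be retained as conversational context". No other treatment of the transcript text before extraction is described.

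**Groups.** Section 2.2 excludes controls with any personal psychiatric history. Section 2.4 recruits patients from outpatient and inpatient care in a psychiatry department.

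**Use.** Section 2.7 states: "For diagnostic discrimination between patients and healthy controls, classification models will be developed and evaluated". AUC is the principal metric. Audio-only and text-only models are compared with multimodal ones, which serves secondary objective iii in section 2.1. Section 2.7 makes the embeddings exploratory and not the primary approach.

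**The concern.** A patient asked about the past week may mention a drug, an admission, a psychiatrist or the diagnosis itself. A control has almost no reason to say any of these about themselves. An embedding represents the content of the text, so a classifier built on it can use such mentions as a proxy for the group label.

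Two results are at stake: the AUC of any text model that uses embeddings, and the apparent gain from adding text to audio. A model that recognises somebody already in psychiatric care says little about supporting a diagnosis, which is the tool's stated purpose. The planned output would not show whether this had happened.

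**Working it through.** **1. The plan's own figure.** Section 2.4 considers "a baseline comparison of 25 patients and 50 healthy controls, with a two-sided significance level of 0.05 and 80% power" and says this "would detect a standardized mean difference of approximately Cohen’s d = 0.70". The normal approximation gives d = (1.960 + 0.842) × √(1/25 + 1/50) = 2.802 × 0.2449 = 0.686. The noncentral t with 73 degrees of freedom gives 0.695. The figure is reproduced. It does not bear on this point, except as a benchmark in step 4.

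**2. Do the stated safeguards remove the cue?**
- *Participant-level splitting and Leave-One-Group-Out validation (2.7)* stop one person's recordings from appearing in both training and test data. A cue shared across patients is learned from the other patients and carries over to the held-out one.
- *Age and sex matching (2.4)* does not concern vocabulary.
- *The caution in 3.1* is about the effect of symptom-focused scale questions on linguistic variables, chiefly sentiment. Both groups get those questions. Self-disclosed patient status is a different mechanism.
- *Shapley attributions (2.7)* on embedding dimensions do not name the words responsible.
- *The public feature matrix (3.2)* will hold neither transcripts nor embeddings, so outside readers could not check afterwards.

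**3. How large could it be?** Let q be the share of patients and f the share of controls who make such a mention. Neither is in the documents, so both are assumed. A yes/no indicator of mention has AUC = 0.5 + (q − f)/2.

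| f (assumed) | q = 20% | q = 40% | q = 60% | q = 80% |
|---|---|---|---|---|
| 0% | 0.60 | 0.70 | 0.80 | 0.90 |
| 2% | 0.59 | 0.69 | 0.79 | 0.89 |
| 10% | 0.55 | 0.65 | 0.75 | 0.85 |

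For example, q = 40% and f = 10% give 0.5 + 0.30/2 = 0.65. These AUCs contain no depressed-language signal at all.

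**4. Added to a genuine signal.** Take a normally distributed feature with d = 0.70. Its AUC is Φ(0.70/√2) = 0.69. Suppose no control makes a mention, mentions are unrelated to the feature among patients, and every mention ranks above every non-mention. Then AUC = q + (1 − q) × 0.69. For q = 20/40/60/80% this gives 0.75/0.81/0.88/0.94. At q = 40%, the rise from 0.69 to 0.81 would look like a gain from text.

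**5. Which variables are exposed?** Apart from the contextual embeddings, the linguistic rows of Table 3 are aggregate scores: polarity, negative-word share, pronoun rate, lexical diversity, word count and sentence length, sentiment variance and coherence. None carries a drug name or a ward as such. They can shift indirectly, for instance if illness words are scored as negative. The direct route is through the embeddings.

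**6. Would a placeholder solve it?** If each such term were replaced by a neutral token, the token would occur in exactly the same transcripts. Its indicator would have the same AUC, 0.5 + (q − f)/2. Repeated tokens could also distort type-token ratio, MTLD and coherence. Removing the utterance avoids the token.

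**The case against.** The strongest reply is that this rests on silence in a condensed article. Nothing says that the transcripts will stay unmasked, and section 2.7 promises full documentation of extraction procedures. This stands in part. The article does fix the text source and gives one purpose for the review, but a reader should not infer that the investigators have decided against masking.

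A reader might also infer that all linguistic features, and so the primary classification model, read the group label. The documents do not support that. The predefined variables are aggregates over a recording of about 10 to 30 minutes, and the embeddings are explicitly not the primary approach.

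Nor do the documents show that most patients will be under treatment, since section 2.2 also admits patients who choose no active treatment. The prompt asks about feelings, and only the scale part of the interview is recorded, so mentions are possible but of unknown frequency. Controls may also speak of a relative's illness or deny taking medication.

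Finally, classifier results are labelled exploratory in sections 2.4 and 2.7. That label tempers how firmly an AUC is read, but it does not tell the reader whether the AUC reflects speech or disclosed care status. Section 2.4 names analytical validity among the study's aims. The within-patient longitudinal analyses do not use the group label and are not affected by this cue.

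**Conclusion.** The point holds in a limited form. Patient-versus-control models that use contextual text embeddings, alone or in a multimodal model, can draw partly on stated patient status. No safeguard in the article removes or measures this. The predefined linguistic variables are exposed only indirectly.

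The size cannot be fixed from the documents. The AUC of 0.55 to 0.90 for a bare mention indicator rests wholly on assumed mention rates (20% to 80% of patients, 0% to 10% of controls). It describes a marker that is not among the planned variables, so it is not an estimate of bias in any planned model. It shows only that the effect could be large enough to change what the unimodal-versus-multimodal comparison supports. This justifies a prespecified sensitivity analysis, not a changed primary analysis.

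**What to change.** - **Flag.** During the manual review already planned, mark utterances in which a participant refers to their own psychiatric diagnosis, psychotropic drugs, ECT or psychotherapy, psychiatric staff or admission. Use one fixed term list in both groups, drawn up and applied blind to model results.
- **Re-run without them.** For every patient-versus-control model that uses text, prespecify a sensitivity analysis with the flagged utterances removed before extraction, not replaced by a placeholder.
- **Report side by side.** Give the AUC and the unimodal-versus-multimodal difference with and without the flagged utterances, together with the AUC of the bare mention indicator and the mention rate in each group.
- **Fix the interpretation in advance.** If the text or multimodal gain disappears after removal, do not attribute it to depressed language.
- **Clarify.** State whether the retained interviewer turns enter the embedding input. If they do, apply the same flagging to them.

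The cost is somewhat more review work and slightly less text in the sensitivity analysis. Data collection and the primary analysis are unchanged. Section 2.10 puts the analysis in February 2028, so the list can still be fixed before any result is seen.
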